## Methods/Design

### Participants

For this observational prospective study, we will analyze patients participating in the SmokeFreeBrain project [58] for a period of 12 months.

The inclusion criteria for the study are patients who are attending the smoking cessation program Smoke Free Brain [59, 60] at the Virgen del Rocio University Hospital, are at least 18 years old, are willing to start treatment to quit smoking, own an Android smartphone and know how to use it, have installed the smoking cessation app recommended by the doctor, and who have not previously had any known adverse effects to the pharmacological treatment.

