**Fig. 2 Fig2:**
[figure not shown]
Screen captures of the message list and the rating mechanism of the “Libre de humos” smoking cessation app. Patients can provide feedback on the messages they receive via the app. They can provide feedback on each message by indicating “like”, “dislike”, or “indifferent”

Each of these topics has a pool of 150 different messages, along with useful tailored information for the patients. These topics and messages have been approved by a smoking cessation psychologist as well as a pulmonologist from the hospital.

Thus, this design will show whether patients prefer the messages selected by the m-HRS at the end of the pilot as a consequence of the HRSA being trained to better match the patient’s preferences, as opposed to the messages sent at the beginning when the HRSA was not configured to learn and improve messages based on the patients’ feedback.

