#### Sending the messages

The frequency at which patients will receive messages is based on the conclusions of Abroms et al. [67] considered in combination with the transtheoretical behavior change model [68]. This model was chosen because the counseling offered at the hospital’s smoking cessation unit is partially based on it, and we wanted the messages to be in line with this counseling. We started considering patients in the preparation phase, which is when they can join the program.Preparation: One message a day until the day of quitting—the topic of these messages is not predicted by the HRSA but chosen at random, and they cannot be rated, so they have no influence on the HRSAAction: Four messages on the day of quitting, and one message a day for the following week.Maintenance: Three messages a week after that, for one year.

In the maintenance phase, as per the transtheoretical behavioral change model, the messages will be sent at random days during the week. In total, a patient who completes the yearlong treatment will receive a total of 150 messages from the m-HRS. The time at which the messages will be sent is also calculated by the HRSA, based on the time difference between when a message is sent and when it is read. The day will be divided in 12 two-hour periods during which the message can be sent at any random time. The sooner the patient reads the message after receipt, the more likely it is that the next message will be sent in the same two-hour period. Patients can deactivate messages during a specific period of time through a do-not-disturb setting. Just like the final decision of the message topic, the messages’ timing is also based on a probability vector.

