### Quality

#### Objective quality

Since the HRSA predicts the message topic and timing of delivery, the objective perceived quality will be measured using two metrics: the precision of the message topics, and how long after receiving the message the users read it.

The precision metric is defined as the relation between the number of hits per message in the first month (baseline) and the extent of “positive”, “neutral”, and “negative” feedback per message in month 3, month 6, month 9, and month 12. Hits are messages with only positive feedback (1) Precision_p_ and with both positive and neutral feedback (2) Precision_p&n_.

1$$ Precisio{n}_P=\frac{\mid \mathrm{m} essages\ with\ positive\ feedback\mid }{\mid all\  messages\ with\  any\  feedback\mid } $$
2$$ Precisio{n}_{p\&n}=\frac{\mid messages\ with\ positive\ and\ neutral\ feedback\mid }{\mid all\  messages\ with\  any\  feedback\mid } $$

We expect the acceptance rate to be higher in month 12, as compared to the previous months, as by this time the HRSA will have more patients and enough information to make accurate decisions.

We will calculate the precision of the system at different points of time, which will reflect the users’ feedback and their interactions with specific sections of the app. All this information is stored in the database of the m-HRS.

The time-to-read metric is defined as the time difference between when the message was sent and when it was read by the user. We will use it to assess the evolution in the quality of the HRSA to predict the best time at which to send a user messages—we theorize that the lesser the time-to-read, the better it is for the user to receive messages at that time.

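### A month-1 to month-12 change in precision cannot be credited to HRSA training alone: time since quitting and message phase change with it, and the origin of month is not stated

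*Protocol article*

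**What the plan says.** **Metric.** In the Protocol article, Objective quality, the definition begins "The precision metric is defined as the relation between the number of hits per message in the first month (baseline" and goes on to "feedback per message in month 3, month 6, month 9, and month 12". No origin is given for these months: it could be study launch, app installation or quit date. Participants says patients will be analyzed "for a period of 12 months", without saying whether that period belongs to the patient or to the study.

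**Expected result.** The same section expects a higher month-12 rate "as by this time the HRSA will have more patients and enough information to make accurate decisions". More patients is a property of the system as calendar time passes.

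**Causal reading.** App features and clinical integration, after Fig. 2, presents the design as a test of whether participants "prefer the messages selected by the m-HRS at the end of the pilot as a consequence of the HRSA being trained". The contrast there is with messages sent "at the beginning when the HRSA was not configured to learn and improve messages".

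**Schedule.** Sending the messages ties delivery to each patient's quit day. Before it, random-topic messages go out that cannot be rated. The action phase is "Four messages on the day of quitting, and one message a day for the following week". Maintenance is three messages a week.

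**Time-to-read.** Objective quality uses its evolution to judge how well the HRSA chooses the sending time. No baseline month is stated for this metric.

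**The concern.** Perceived quality is a primary outcome, and the change in precision over time is the evidence offered that the HRSA learns. That change is read as an effect of training, but there is no concurrent comparison group, and two other things move along the same axis: how long ago the patient quit, and which message phase the patient is in. If patients rate messages differently in the quit week than months later, precision will rise or fall with no learning at all.

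The unstated origin makes this worse.
- If months are counted per patient, having more patients is not a property of a given patient's month 12. A late entrant's month 1 is also served by an HRSA already informed by earlier patients, since demographic similarity is one of its inputs.
- If months are counted from launch, month 1 holds only new quitters, and month 12 holds mostly patients long past quitting.

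The result could therefore be reported as evidence that the algorithm works when it shows only that quitters change over a year, or a real gain could be masked.

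**Working it through.** **The plan's own figures.** Sample size gives 60 × 150 = 9000 messages, which reproduces. The 150 per completer does not follow from the schedule. Action phase 4 + 7 = 11; with maintenance to day 365, 11 + 3 × 357/7 = 164; with 52 full weeks of maintenance, 11 + 156 = 167. Maintenance alone to day 365 gives 153. Those statements need reconciling, but nothing below depends on the total.

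**Inputs from Sending the messages.** 11 rateable messages in the 8 days from the quit day, then 3/7 a day. Preparation messages cannot be rated, so they do not enter precision. A month is taken as 30 days, and the counts are of rateable messages sent.

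**Origin = quit day.**
- Month 1: 11 + 3 × 22/7 = 20.4; action share 11/20.4 = 54%.
- Months 3, 6, 9, 12: 3 × 30/7 = 12.9 each; action share 0%.
- Ratio of volumes: 20.4/12.9 = 1.6.

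**Origin = installation**, with an assumed preparation period of P days. Month 1 holds 11 + 3 × (22 − P)/7 rateable messages for P up to 22.

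| P (assumed) | Rateable in month 1 | Action share |
|---|---|---|
| 0 | 20.4 | 54% |
| 7 | 17.4 | 63% |
| 14 | 14.4 | 76% |
| 21 | 11.4 | 96% |
| 30 | 0 | undefined |

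**Origin = study launch**, assuming quit days spread evenly and no dropout. With one new quitter a day and accrual still open, day d after launch (d ≥ 7) carries 11 action messages and 3/7 × (d − 7) maintenance messages.
- Month 1 (days 0–29): action (4 + 5 + … + 11) + 22 × 11 = 60 + 242 = 302; maintenance 3/7 × 253 = 108.4; action share 302/410.4 = 74%.
- Month 3: 330/(330 + 867.9) = 28%.
- Month 6: 330/(330 + 2025) = 14%.
- Month 12, accrual open all year: 330/(330 + 4339) = 7%. If accrual lasts 3 to 11 months, the month-12 share is 0 to 1%.
- Mean time since quitting, weighted by messages and for accrual of 3 to 11 months: about 5 days in month 1, and 178 to 299 days in month 12.

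**What phase mix alone could do (illustration only).** The article gives no rating rates by phase. Take the quit-day origin, no learning, and precision (positive ratings only) of 0.50 in action and 0.60 in maintenance. The baseline is (11 × 0.50 + 9.43 × 0.60)/20.43 = 0.546. Month 12 is 0.600, an apparent gain of 5.4 points. Swapping the two values gives a loss of 5.4 points; 0.40 against 0.60 gives a gain of 10.8.

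**The case against.** The best defence is that a journal article may leave month windows and adjustment to a fuller document, that the first goal is framed as description, and that the authors already urge caution. Background raises the novelty effect, Discussion warns against simplistic conclusions, and Limitations concedes that the HRSA cannot distinguish changes of interest during cessation. The first part has some force: an unstated origin alone would be minor. But the contrast is affected whichever origin is chosen, and the article itself states the causal reading. The cautions offer no way to separate learning from quit stage, and they leave that reading in place.

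Four further objections do stand and limit the point:
- Precision is a ratio, so 1.6 times the volume does not shift it mechanically. No bias has been shown, only a route for one.
- A late entrant's month 1 still lacks that patient's own ratings, so it remains a low-information period for individual learning.
- Starting the baseline at maintenance drops the messages sent when the HRSA knows least about the patient, and so may hide early learning.
- Staggered entry separates cohort-level learning from time since quitting only if entry cohorts are comparable. Learning from a patient's own ratings rises with time since quitting and cannot be separated this way.

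**Conclusion.** The concern holds: on any origin, month 1 and month 12 differ in time since quitting and message phase as well as in HRSA training. From the quit day, the action share of rateable messages is 54% against 0%. From launch it is about 74% against 0 to 7%, depending on the assumed accrual. The resulting bias in precision is unknown in size and direction.

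A reader might infer more than the article supports:
- *That the baseline is defined on two clocks.* It is not. The origin is left unstated, and a system-time reason is given for windows that fall on a patient-time schedule.
- *That later months always carry three messages a week.* This is so only from the quit day, or from installation once the action phase is over. From launch, months 3 and 6 may still contain action messages from new entrants.
- *That time-to-read uses the same first-month baseline.* The article states that baseline for precision only. The same caution applies to reading the evolution of time-to-read as HRSA quality.

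**What to change.** 1. Count months from each patient's quit day, and say so.
2. Report precision and time-to-read separately for action and maintenance messages.
3. Add a like-for-like contrast: the first 30 days of maintenance against months 3, 6, 9 and 12. Keep the full first-month contrast beside it.
4. For the claim about more patients, compare patients at the same time since quitting according to calendar date or cumulative cohort ratings at sending. A message-level model with both terms would also serve, but it would be new to the plan. State that either approach relies on comparable entry cohorts and cannot isolate learning from a patient's own ratings.
5. Reword the paragraph after Fig. 2 so that a month-1 to month-12 difference is a change over time and not a consequence of training alone.

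**Cost.** No new data collection: ratings are stored, quit dates are loaded from the health record, and send and read times already drive the HRSA. There is some added analysis. The like-for-like baseline is smaller and may understate early individual learning, which is why the full contrast stays.

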### Sample size

We aim to recruit 120 patients. No power analysis was done for this study, as we followed a convenient sample [73] method: our recruiting partner Hospital Virgen del Rocío estimated they could only access 120 patients within the time limits of the project. The expected dropout rate is 50%. This means the system will have sent at least 9000 messages to patients before the study ends (a minimum of 60 patients ending the treatment multiplied by 150 messages sent throughout the treatment).

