## Discussion

This study will explore how patients enrolled in a smoking cessation program perceive and engage with an m-HRS that sends them periodic motivational messages encouraging them to stop smoking. We also expect the m-HRS to help increase the low attrition rate that is typically seen in eHealth trials [74].

The answers to this study’s research questions will benefit future recommender system-based behavioral change interventions. Researchers will be able to re-use our proposed perceived quality and engagement metrics and exploit the knowledge derived in order to design new and improved health recommender systems that take into account user appreciation and engagement. Thus, the health messages sent to the users will be more interesting, relevant, and engaging for them.

We expect the patients’ perceived quality of the system to increase over time, that is, for the precision of the messages to increase and the patients’ time to read the messages to decrease. However, we should consider that, at some point during the intervention, patients may stop reading the messages because they have uninstalled the app. This may be because they have successfully quit smoking and do not want any smoking-related reminders, because they have relapsed, or because they never engaged with the app in the first place and have decided to remove it from their smartphone. Therefore, these metrics will need to be carefully analyzed to avoid simplistic conclusions.

The users’ in-app activity analytics will provide an insight into how patients react to the messages the HRSA selects for them. This opens up several future research opportunities, such as comparing whether the theoretical interests patients claim to have are in fact their interests, noting the time they stop rating messages because they are no longer interested in receiving more messages, and having an initial m-HRS-generated message patient acceptance data report for future implementation in smoking cessation programs.

However, this study may suffer from the trust problem like all recommender agents. Despite the elaborate design of the HRSA, should a patient receive a single message that is out of context, it may ruin her confidence in the system and she may stop using the m-HRS altogether [75]. In order to minimize this, the messages have been designed such that they are applicable to almost all circumstances and experiences of a patient.

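### Time-to-read has no common read window, so if logging closes near month 12 its mean can fall late in the year without any improvement in message timing

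*Protocol article*

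**What the plan says.** Under Objective quality, time-to-read is one of two objective measures of perceived quality, which is a primary outcome: "The time-to-read metric is defined as the time difference between when the message was sent and when it was read by the user". The article sets no maximum delay and no rule for a message that is still unopened when data collection ends. It does not name a summary statistic.

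The use of the metric is stated next: "We will use it to assess the evolution in the quality of the HRSA to predict the best time". The Discussion gives the expected direction, which is for patients' "time to read the messages to decrease".

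On follow-up, Participants says "we will analyze patients participating in the SmokeFreeBrain project [58] for a period of 12 months". Under Sending the messages, the action phase is "Four messages on the day of quitting, and one message a day for the following week", followed by "Maintenance: Three messages a week after that, for one year". Messages therefore go out up to the end of the stated observation period. The article does not say when read logging stops.

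**The concern.** An open-ended delay can be observed only if it is shorter than the time left before logging ends. That time shrinks through the year. A month-1 message opened ten weeks later enters the data with its full delay. The same behaviour in month 12 produces no observation if logging has closed. Late opening is possible in this app: the caption of Fig. 2 describes a message list, and Choosing the message topic counts re-read messages as a sign of interest.

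This is separate from slow or disengaged patients leaving. It can arise when every patient stays and nobody's habits change. It also runs in the direction that the authors predict, so part of a late fall could be credited to the algorithm when it comes from the length of observation.

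**Working it through.** **The plan's own figure.** None is given for time-to-read. The nearest calculation, in Sample size, reproduces: 120 × 0.50 × 150 = 9000 messages. It does not bear on this point.

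**Inputs from the article.** Twelve months of observation, taken as 365 days; messages sent throughout; delay = read time minus sent time, for read messages only.

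**Inputs assumed, because the article gives none.** The distribution of delays, the summary statistic and the closing day of the log.

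**Time left to be read if the log closes at day 365** (month = 365/12 days):

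| Month sent | Days left, range | Mean |
|---|---|---|
| 1 | 335–365 | 350 |
| 3 | 274–304 | 289 |
| 6 | 182–213 | 198 |
| 9 | 91–122 | 106 |
| 12 | 0–30 | 15 |

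**Formula.** A message sent on day s is observed only if its delay T ≤ c, with c = 365 − s. The observed mean is E[T | T ≤ c]. It cannot rise as c shrinks, and it falls once some delays exceed c. For an exponential delay with mean μ, the numerator is μ − (μ + c)e^(−c/μ) and the denominator is 1 − e^(−c/μ). For a mixture of prompt and late reads, weight each part by its share.

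**Worked example.** 90% of messages read with mean 4 h (0.167 d), 10% with mean 30 d.
- c = 350: (0.9 × 0.167 + 0.1 × 30.0)/1.00 = 3.15 d = 75.6 h.
- c = 15: late numerator 30 − 45 × 0.607 = 2.71; late denominator 0.393. So (0.150 + 0.271)/(0.900 + 0.039) = 0.448 d = 10.7 h. Over the whole of month 12 (c from 0 to 30) the mean is 12.0 h.

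**Results at day-365 closure**, same delay distribution in every month (simulation, 1,000,000 messages per month):

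| Assumed reading habit | Month 1 mean | Month 9 | Month 12 | Change, 1 to 12 |
|---|---|---|---|---|
| All prompt, mean 4 h | 4.0 h | 4.0 h | 4.0 h | −0.5% |
| 2% late, mean 14 d | 10.7 h | 10.6 h | 6.0 h | −44% |
| 5% late, mean 30 d | 40.1 h | 35.0 h | 7.9 h | −80% |
| 10% late, mean 30 d | 75.6 h | 66.1 h | 12.0 h | −84% |
| 10% late, mean 60 d | 144.2 h | 80.9 h | 9.1 h | −94% |
| Lognormal, median 4 h, σ 1.5 | 12.3 h | 12.3 h | 10.9 h | −11% |
| Lognormal, median 4 h, σ 2.5 | 65.3 h | 48.9 h | 21.7 h | −67% |

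Months 1 to 6 are nearly flat unless the tail is long. Medians move little: 3.24 to 2.92 h with 10% late at 30 d, and at most 4.00 to 3.33 h (lognormal, σ 2.5). Adding 50% dropout to the 10%/30 d case gives 68.7 to 11.9 h, so the effect remains.

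**Sensitivity to log closure** (90% prompt with mean 6 h, 10% late with mean 30 d; month-1 mean 3.2 d):
- closure at day 365: −82%
- closure at day 395: about −51%
- closure at day 455: −13%

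With a lighter tail of 5% late at mean 7 d, the fall is 26% at day 365 and 1% at day 395. With 1% late at mean 7 d it is about 10% at day 365 and close to nil at day 395.

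**With a common 7-day window**, using only messages observed for the full 7 days, months 1 and 12 agree in every row of the table (for example 5.7 and 5.7 h for 10%/30 d, among messages read within the window). The 7-day restricted mean in the 6 h case is 0.9 × 0.25 + 0.1 × 30 × (1 − e^(−7/30)) = 0.225 + 0.624 = 0.85 d in any month.

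**The case against.** Three inputs that determine the size are not in the article: the use of a mean, closure of the log at each patient's day 365, and a tail of late reads. A median would nearly remove the effect. Reads are sent to a hospital server, and nothing says that logging stops on each patient's anniversary. If recruitment were staggered and the data locked once, 12 months after the last entry, the 10%/30 d fall would be 41%, 23% or 11% for recruitment over 90, 180 or 365 days. The fixed comparison of months 1, 3, 6, 9 and 12 is set out for precision; for time-to-read the article speaks only of evolution. A condensed article may also leave the summary statistic and data cut-off to a fuller document.

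All of this limits the size, and it stands. A reader might infer that mean time-to-read must fall by construction, or that a fall of about 82% is to be expected. The documents support neither.

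What remains is the definition and how it is to be interpreted, and both are stated. An open-ended delay is not comparable between early and late messages unless a window is added. The Discussion's caution about these metrics is prompted by patients uninstalling the app and supplies no rule that would deal with this. Reporting the share of messages read per user, under Engagement at an individual level, does not repair the delay metric either.

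**Conclusion.** The concern holds as a conditional one. If logging closes at or soon after month 12 and the summary is sensitive to long delays, time-to-read can fall late in the year with no learning. The direction follows from the definition. The size does not: it runs from about nil, when nearly all reads are prompt or a short tail meets later closure, to 80% or more at day-365 closure when 5 to 10% of messages are read on average a month or more late. The fall is concentrated in month 12, although with a 60-day tail month 9 is already 44% lower (144.2 to 80.9 h). A median is little affected. The change is worth making before the data are seen, because the choice of summary or closing date could decide whether a fall is read as success.

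**What to change.** Define time-to-read within one window that is the same for every message, for example 7 days from sending. Treat a message unread by then as censored at the window. Include only messages for which the full window was observed, or keep logging for one window after the last message. Compare months on the proportion read within a fixed time, for example 24 hours, and on the restricted mean or the median. State the summary statistic and the date on which logging closes.

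No new data are needed, since the metric already requires send and read times. The cost is that delays beyond the window are no longer distinguished. If logging closes at day 365 and is not extended, up to about 23% of month-12 messages are dropped (7/30.4).

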### Outcomes

Our primary outcomes are the patients’ perceived quality of the m-HRS and their engagement with it. We define quality as a set of features that makes the system recommend timely and relevant messages for each patient. As no formal methodology has yet been used to assess the quality of and engagement with HRS, we will use both objective and subjective quality measures along with engagement metrics at an aggregated and individual level.

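### Time-to-read exists only for messages that are read, so its change over the year mixes the algorithm's timing with a change in who is still reading

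*Protocol article*

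**What the plan says.** Perceived quality is one of two primary outcome domains (Outcomes section): "Our primary outcomes are the patients’ perceived quality of the m-HRS and their engagement with it". Time-to-read is one of the two objective quality metrics. The Objective quality section defines it thus: "The time-to-read metric is defined as the time difference between when the message was sent and when it was read by the user". The purpose follows: "We will use it to assess the evolution in the quality of the HRSA to predict the best time at which to send a user" messages. The direction of interpretation is also fixed: "we theorize that the lesser the time-to-read, the better it is for the user to receive messages at that time".

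The Discussion says that perceived quality should rise over time, that is, "for the precision of the messages to increase and the patients’ time to read the messages to decrease". It adds that "patients may stop reading the messages because they have uninstalled the app", gives successful quitting, relapse and lack of engagement from the start as possible reasons, and asks for care in interpreting the metrics. The Sample size section states "We aim to recruit 120 patients" and "The expected dropout rate is 50" per cent.

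Unread messages are counted in one place. Under Engagement at an individual level, the read rate is each user's messages read divided by messages sent. It has no stated time points and no link to time-to-read.

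**The concern.** The metric is conditional on reading. A message that is never opened has no read time, and the article assigns it no value, censoring limit or fixed set of patients. A comparison of an early month with a late month is then a comparison of two different groups of readers. If the groups differ in habitual reading speed, the metric shifts with no change in how well the algorithm chooses the sending time. One of the two objective quality measures could then show the expected fall, and that fall could be credited to the algorithm, when only the composition of the readers has changed.

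**Working it through.** **The plan's own figure.** 120 × (1 − 0.50) = 60 completers, and 60 × 150 messages = 9000, as the Sample size section states. The article gives no reading times, no standard deviations and no relation between speed and stopping. Everything below assumes these, with 50% overall loss and **no change in any patient's reading speed**.

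**Two-group mean.** Take 60 fast readers (1 h) and 60 slow readers (4 h). Month 1 mean = (60×1 + 60×4)/120 = 2.5 h. Month 12 mean = (n_fast×1 + n_slow×4)/(n_fast + n_slow), over those still reading.

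| Stop: fast / slow | Still reading: fast / slow | Month 12 mean | Change |
|---|---|---|---|
| 50% / 50% | 30 / 30 | 150/60 = 2.50 h | 0% |
| 35% / 65% | 39 / 21 | 123/60 = 2.05 h | −18% |
| 20% / 80% | 48 / 12 | 96/60 = 1.60 h | −36% |
| 0% / 100% | 60 / 0 | 60/60 = 1.00 h | −60% |
| 65% / 35% | 21 / 39 | 177/60 = 2.95 h | +18% |

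The last row shows that the sign reverses if prompt readers are the ones who leave.

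**Simulation.** Log-normal reading times, overall median 3 h, within-patient log-SD 1.0, between-patient log-SD 0.5 or 1.0. The odds of stopping are multiplied by 1, 2 or 4 per SD of slowness; 200,000 simulated patients per setting.

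| Between-patient log-SD | Odds ratio | Median, month 1, all | Median, month 12, readers | Change | Month 1 median, same continuing readers |
|---|---|---|---|---|---|
| 0.5 | 1 | 3.00 h | 3.00 h | about 0% | 3.00 h |
| 0.5 | 2 | 3.00 h | 2.57 h | −14% | 2.55 h |
| 0.5 | 4 | 3.01 h | 2.34 h | −22% | 2.34 h |
| 1.0 | 1 | 3.02 h | 2.97 h | about 0% (−1.6%, simulation noise) | 3.01 h |
| 1.0 | 2 | 3.01 h | 2.22 h | −26% | 2.20 h |
| 1.0 | 4 | 3.01 h | 1.81 h | −40% | 1.82 h |

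The fourth and last columns agree closely in every row: comparing the same continuing readers gives about zero change, which is the truth in this set-up.

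**Keeping unread messages in the denominator.** If those who stopped are still sent messages, the share of all sent messages read within 2 h goes from about 36–39% in month 1 to about 18–27% in month 12. The false improvement disappears, but a fall appears that reflects stopping rather than worse timing. The all-sent share alone therefore does not measure timing quality either.

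**The case against.** Four counter-arguments deserve weight.

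- *The article is silent, and handling of unread messages can sit in an analysis plan.* It names no mean, median or model, so no particular summary can be called the plan's. This stands. But the definition and its interpretation are fixed in the article, and they are what create the ambiguity.
- *The Discussion recognises the problem.* It does, and the authors should be credited with foreseeing non-reading. The caution sets no rule, however, and leaves the definition unchanged.
- *The read rate and rolling retention would show people leaving.* They would show that reading fell. They would not say how much of a change in time-to-read came from that fall.
- *Direction and size are assumed.* This stands. The Discussion's reasons for uninstalling include successful quitting, which has no stated link with reading speed.

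A reader might infer more: that the metric is bound to favour the expected result, or will show better timing while reading gets worse. A case can be built. Let half the messages go to readers with a 2 h median and half to readers with a 24 h median (exponential times). Then let every slow reader stop, no prompt reader stop, and prompt readers slow to 3 h. The median among read messages falls from about 5.5 h to 3.0 h. The share of sent messages read within 2 h falls from 0.5×0.5 + 0.5×(1 − 2^(−2/24)) = 27.8% to 0.5×(1 − 2^(−2/3)) = 18.5%. The arithmetic is right but the case is extreme. With prompt readers left at 2 h, the share falls only to 0.5×0.5 = 25.0%; the rest comes from the added slowing. The documents support neither the split nor the slowing, and do not say that dropouts go on being sent messages.

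**Conclusion.** The concern holds in a limited form. As defined, a change in time-to-read over the year cannot be attributed to the algorithm's timing, because a change in who is still reading would look the same. With 50% loss and the assumed distributions, selection alone moves the median by between about 0% and −40%. The fall requires slower readers to stop more often, which is plausible but not stated. Stopping unrelated to speed gives about no bias, and prompt readers leaving first would push the metric up. The documents do not support the claim that the metric is certainly biased towards the expected result or that it rewards non-reading.

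Severity: should-fix. It affects one of two objective measures within a primary outcome, in an exploratory observational study with no stated hypothesis test for it.

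**What to change.** 1. Analyse time-to-read as time-to-event over all messages sent to patients who still have the app installed. Censor unread messages at a fixed limit (for example 72 h) and treat patient as the cluster.
2. Draw the conclusion on timing quality from a within-patient comparison of month 1 with later months among continuing readers, and define that group in advance.
3. Report beside it, by month, the read rate and the share of all sent messages read within a fixed time of sending. For example, use 2 h from sending rather than the same clock window: messages go out at a random moment within a two-hour period, so one sent late would have only minutes to count.
4. Keep any mean or median among read messages as descriptive only.

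Cost: a little more analysis and a few sentences of wording. The algorithm already uses the sent-to-read interval (Sending the messages section), and the read rate already needs counts of sent and read messages. The article does not say whether uninstalling is recorded for each patient; if it is not, a proxy such as the last contact with the hospital server has to be fixed beforehand. The within-patient result applies only to continuing readers, which is why the all-sent share and read rate must stand next to it.
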